## Analysis of secondary endpoints

The prognostic value/accuracy of FDG/FLT-PET regarding clinical failure, SD and clinical response in NSCLC patients treated with erlotinib will be compared by ROC analysis; optimal cut-off values for FDG/FLT PET will be chosen (*secondary objective*).

Association between EGFR mutation, KRAS mutation and EGFR positivity with clinical response will be tested by Fisher's exact test.

Secondary endpoints (FFTF and OS) will be analyzed using descriptive statistics after at least one year follow-up of all patients.

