## 2 AIM OF TRIAL

Based on the survival benefit demonstrated in patients with relapsed NSCLC (Shepherd et al., 2005) as well as on its favourable toxicity profile compared to chemotherapy the EGFR-TKI erlotinib represents an attractive candidate to be included also in protocols for the first line treatment of NSCLC. Accordingly, preliminary data from phase II trials show promising response rates for erlotinib treatment in the first line setting (Giaccone, 2005). In parallel, in the near future further targeted drugs will be available for NSCLC treatment. For instance, the addition of the anti-VEGF monoclonal antibody bevacizumab has recently shown to prolong survival when added to standard chemotherapy as first line treatment of NSCLC. Thus, in order to optimize the choice and the sequence of new drugs in NSCLC treatment, an early identification of patients with no clinical benefit, i.e. patients with progressive disease under treatment, is desirable. In the ERLOPET trial, we aim at establishing PET analysis as a tool for early identification of NSCLC patients with no clinical benefit from monotherapy with erlotinib as first line treatment. A pre-treatment computed tomography (CT) scan will be performed for evaluation of the patients' individual tumor burden. FDG- and FLT-PET scans will be performed between d -10 and d1 (but prior to therapy) for identification of pre-treatment PET status. Between d7 and d14, FDG- and FLT-PET scans will be performed for the early identification of erlotinib non responders. The imaging procedures will be performed at different days, i. e. one procedure per day. After six weeks of treatment, final response evaluation will be performed using CT, FDG- and FLT-PET scans. These results will be correlated to the mutational status of the EGFR - and the KRAS gene and the expression of EGFR in pretreatment samples.

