##### **Secondary Objectives**

1. To identify PET characteristics for progressive disease following erlotinib treatment (changes in SUV during treatment)
2. To identify PET characteristics for response to erlotinib (changes in SUV during treatment)
3. To identify PET characteristics for stable disease following erlotinib treatment (changes in SUV during treatment)
4. To confirm the statistical association of EGFR mutational status and clinical response in NSCLC patients treated with erlotinib
5. To confirm the statistical association of KRAS mutational status and clinical resistance to treatment of NSCLC patients with erlotinib
6. To determine the discriminatory capability of FDG-/FLT- PET regarding EGFR and KRAS mutational status in NSCLC patients
7. To compare prognostic value of FDG-PET, FLT-PET and EGFR mutational status regarding clinical response in NSCLC patients treated with erlotinib
8. To identify EGFR and KRAS sequence characteristics for clinical response and stable disease following erlotinib treatment
9. To assess safety of Erlotinib
10. To determine response rates
11. To determine rates of stable diseases
12. To determine one-year FFTF
13. To determine one-year OS
14. To determine median overall survival time

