## Analyses of primary endpoints

1. The prognostic value/accuracy of FDG-/FLT-PET regarding non-progression in NSCLC patients treated with erlotinib will be evaluated by ROC analysis (area under the ROC curve, AUC);  $H_0: AUC_{\text{FDG/FLT PET}} \leq 0.5$ ,  $H_A: AUC_{\text{FDG/FLT PET}} > 0.5$  (intersection-union test at one-sided level 2.5% – *primary objective*).

2. The statistical association of EGFR respectively KRAS mutational status, EGFR positivity and clinical response in NSCLC patients treated with erlotinib will be evaluated by Fisher's exact test (at one-sided level 2.5%; strong type 1 error control is maintained if analysis of item 1 was significant – *secondary objective*).

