## Sample size calculation

Assumptions:

- (1) 10% responder, 60% progressers; thus 40% non-progressers
- (2) Primary variable is the 'area under the ROC curve (AUC,  $\vartheta$ )', (PET-values of non-progressers > progressers)
- (3) Variability in the PET-results of non-progressers is greater than that of progressers
- (4) Type-I-error 0.05; type-II-error 0.20
- (5) True accuracy (AUC) is at least 0.70 (alternative hypothesis; some common diagnostic tests have an AUC greater than 0.70 [1; p29])

Sample size calculation:

| AUC ( $\vartheta$ ) | # Non-progressers | # progressers | # Total   |
|---------------------|-------------------|---------------|-----------|
| 0.70                | 26                | 38            | 64        |
| 0.75         | 16         | 24     | 40 |
| 0.80                | 11                | 16            | 27        |

Note: The sample size was calculated using formulae (6.3) and (6.6) in [Zhou et al., 2002; p199, 201].

Thus, assuming  $\vartheta_1 = 0.75$ , 40 patients are needed to reject the null hypothesis  $H_0: \vartheta = 0.5$  in favour of the alternative  $H_1: \vartheta \neq 0.5$ . The sample size will be sufficient to yield a 95% confidence interval for  $\vartheta$  with width  $2 \times 0.17 = 0.34$ .

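### Optimal PET cut-offs are to be chosen in the trial's only 40 patients; sensitivity and specificity reported at them without correction would be too high

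*Protocol*

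**What the plan says.** Section 7.2, under the analysis of secondary endpoints, compares the accuracy of FDG- and FLT-PET for clinical failure, stable disease and response by ROC analysis and adds that "optimal cut-off values for FDG/FLT PET will be chosen". The step is tagged as a secondary objective. No optimality criterion is named.

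The primary analysis in the same section is of a different kind. Prognostic accuracy for non-progression "will be evaluated by ROC analysis (area under the ROC curve, AUC"), with an "intersection-union test at one-sided level 2.5" per cent.

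The sample size section assumes "10% responder, 60% progressers; thus 40% non-progressers" and concludes that "40 patients are needed to reject the null hypothesis" if the true AUC is 0.75. Its table splits the 40 into 16 non-progressers and 24 progressers. Section 3.1 describes a single-centre, single-arm, exploratory phase II study, and section 3.2 caps recruitment at 40.

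On purpose, section 2 states that "we aim at establishing PET analysis as a tool for early identification of NSCLC patients with no clinical benefit from monotherapy" with erlotinib. The first secondary objective in section 3.1 is "To identify PET characteristics for progressive disease following erlotinib treatment (changes in SUV during treatment").

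The protocol gives no SUV threshold fixed in advance, describes no second cohort and mentions no resampling. The external review in section 7.4 concerns the imaging findings and does not validate a cut-off.

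**The concern.** A cut-off that maximises a criterion in a sample is fitted partly to that sample's noise. Sensitivity and specificity read from the same patients are therefore too favourable on average, and the effect is large when one group has 16 patients and the other 24. It is larger for a response cut-off, because 10% of 40 is only about 4 responders.

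The aim in section 2 is an early identification tool. An AUC shows that a marker discriminates, but a decision about one patient needs a threshold. A reader who wants to use the result would look at the cut-off and its apparent accuracy.

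Secondary objective 7 also compares PET with EGFR mutational status. A mutation call has no tuned threshold. If PET entered that comparison at its optimised cut-off, the optimism would favour PET only.

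**Working it through.** **Inputs from the protocol.** 16 non-progressers and 24 progressers; AUC 0.75 against 0.5; "Type-I-error 0.05; type-II-error 0.20"; 10% responders, so about 4 of 40. Section 7.3 (sample size) says that non-progressers are the more variable group but gives no figure.

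**Assumptions made here.** Normally distributed PET values; cut-off at the maximum of the Youden index (sensitivity + specificity − 1, with sensitivity referring to non-progressers and specificity to progressers); equal SDs in the base case, and a non-progresser SD 1.25 and 1.5 times larger as alternatives.

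**Step 1: reproduce the plan's sample size.** Use the binormal variance V(AUC) = 0.0099·exp(−a²/2)·[(5a² + 8) + (a² + 8)/R], with a = 1.414·z(AUC) and R = 24/16 = 1.5.
- V(0.5) = 0.0099 × (8 + 8/1.5) = 0.132.
- For AUC 0.75, a = 1.414 × 0.6745 = 0.954 and V = 0.116.
- n = [1.96·√0.132 + 0.842·√0.116]² / 0.25² = 15.97, so 16 non-progressers, 24 progressers and 40 in total.
- The 95% half-width is 1.96·√(0.116/16) = 0.167, which matches the stated 0.17.
- The other rows also match: 63.5 for AUC 0.70 (stated 64) and 26.9 for AUC 0.80 (stated 27).

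The plan's own figures are sound. They concern the AUC only.

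**Step 2: optimism of an optimal cut-off with 16 versus 24.** In 20,000 simulated trials per scenario, the cut-off was chosen at the maximum empirical Youden index. Its in-sample performance was then compared with the true performance of the same cut-off. At AUC 0.75:

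| | In sample | True | Difference |
|---|---|---|---|
| Non-progressers correct | 0.76 | 0.67 | 0.09 |
| Progressers correct | 0.72 | 0.66 | 0.06 |
| Youden index | 0.48 | 0.34 | 0.15 |
| Overall accuracy | 0.74 | 0.67 | 0.07 |

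Differences are taken before rounding. The apparent Youden index exceeded the true one in about 90% of the simulated trials.

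**Step 3: sensitivity to the assumptions.**
- Youden optimism by true AUC: 0.18 at 0.50, 0.16 at 0.70, 0.15 at 0.75, 0.14 at 0.80, and 0.11 to 0.12 at 0.90. The spread at 0.90 depends on where between two observed values the cut-off is placed.
- With a larger non-progresser SD at AUC 0.75: 0.144 (ratio 1.25) and 0.136 (ratio 1.5).
- Response cut-off, 4 versus 36: about 0.25 to 0.26 at AUC 0.75 and 0.21 at 0.90. With the cut-off midway between observed values it is 0.19 at 0.95 and 0.16 at 0.98.

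**Step 4: how much a correction recovers.** In 600 simulated trials at AUC 0.75, with 150 bootstrap resamples each and the cut-off search repeated in every resample, the mean Youden index fell from 0.481 to 0.385, against a true 0.336. The share of bias removed is (0.481 − 0.385)/(0.481 − 0.336) = 0.096/0.145, about two thirds.

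**The case against.** The strongest reply is that the criterion, resampling and optimism correction are details commonly left to a statistical analysis plan, which is not available here. That stands in part. The protocol's silence does not show that no correction is planned, and a reader should not infer that. But an analysis plan cannot supply a validation cohort that the design lacks, and the protocol does commit to data-driven selection in its one cohort.

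A reader might also infer that the trial will overstate its PET rule or will recommend a threshold for practice. The documents do not support that. Nowhere do they say that sensitivity or specificity at the cut-off will be reported, tested or put forward for use. The point is therefore conditional on such reporting, although it is the natural use of a chosen cut-off.

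Nor is the trial's main accuracy claim biased. The primary test, the sample size and the nonparametric ROC method all rest on the AUC. The cut-off step is secondary, in a trial labelled exploratory.

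On size, 0.15 is the sum of two errors. For progressers alone, the patients whom section 2 wants to identify, the optimism is about 6 points. For response, section 7.3 expects a nearly complete association with SUV reduction, so the lower end of the 0.16 to 0.26 range may apply. Both remarks stand, and neither removes the bias.

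**Conclusion.** The concern holds in a limited form. Choosing optimal cut-offs and reading their accuracy in the same 16 and 24 patients gives figures that are too favourable on average. At AUC 0.75 the excess is about 0.15 on the Youden scale, that is, 9 points for non-progressers and 6 points for progressers. Across AUC 0.90 down to 0.50 it is about 0.11 to 0.18, and for a response cut-off about 0.16 to 0.26 (AUC 0.98 down to 0.75).

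This matters only if the uncorrected values are reported. It leaves the primary AUC analysis and the sample size untouched. The sizes rest on normal markers and the Youden criterion, neither of which the protocol specifies. The direction held for every AUC and SD ratio tried.

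**What to change.** Amend the cut-off sentence in section 7.2 to state that:

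- the chosen cut-offs are exploratory;
- sensitivity and specificity at each cut-off are reported both uncorrected and optimism-corrected, by bootstrap or cross-validation that repeats the cut-off search in every resample;
- the correction is partial (about two thirds of the bias in the bootstrap simulation above; cross-validation was not examined);
- a cut-off needs confirmation in independent patients before it is used.

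This needs no extra patients and no change to the primary analysis or the sample size. The cost is slightly more analysis work and less favourable reported accuracy.

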## Statistical Reporting

The final statistical report will be done by [name] and included also in the final report of the study.

## 7.3 Further analyses

### Subsequent analyses

### Expected results

Based on the results of clinical trials with erlotinib in NSCLC patients in Western Europe and the US, we expect about 10% of patients with response (CR, PR) to treatment with erlotinib, about 30% with stable disease and about 60% with progressive disease. Furthermore, we expect about 90% of patients with mutated EGFR responding to therapy. KRAS mutations and EGFR mutations are expected to be nearly exclusive.

Based on published PET data, especially from patients with GIST treated with imatinib, we expect a nearly 100% association of clinical response (CR, PR in CT after 6 weeks of treatment) and reduction in SUV (PET analyses on days 8,9).

### Expected flow of information

For the expected patient population similar response rates as described in published studies for Western World patients are expected.

## Sample size calculation

Assumptions:

- (1) 10% responder, 60% progressers; thus 40% non-progressers
- (2) Primary variable is the 'area under the ROC curve (AUC,  $\vartheta$ )', (PET-values of non-progressers > progressers)
- (3) Variability in the PET-results of non-progressers is greater than that of progressers
- (4) Type-I-error 0.05; type-II-error 0.20
- (5) True accuracy (AUC) is at least 0.70 (alternative hypothesis; some common diagnostic tests have an AUC greater than 0.70 [1; p29])

Sample size calculation:

| AUC ( $\vartheta$ ) | # Non-progressers | # progressers | # Total   |
|---------------------|-------------------|---------------|-----------|
| 0.70                | 26                | 38            | 64        |
| 0.75         | 16         | 24     | 40 |
| 0.80                | 11                | 16            | 27        |

Note: The sample size was calculated using formulae (6.3) and (6.6) in [Zhou et al., 2002; p199, 201].

Thus, assuming  $\vartheta_1 = 0.75$ , 40 patients are needed to reject the null hypothesis  $H_0: \vartheta = 0.5$  in favour of the alternative  $H_1: \vartheta \neq 0.5$ . The sample size will be sufficient to yield a 95% confidence interval for  $\vartheta$  with width  $2 \times 0.17 = 0.34$ .

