#### **3.2 Recruitment**

It is planned to recruit a maximum of 40 patients over a 15 months period.

Patients will be recruited after screening only if all inclusion criteria are met, no exclusion criteria are met and written informed consent has been obtained. No difference in recruitment concerning gender will be applied. According to the distribution of NSCLC more male than female study participants are expected.

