### **Inclusion in the analysis**

Full analysis set (primary analysis, intention-to-treat): All patients included in the study will be analysed (contingent on availability of endpoints). Per-protocol set (secondary analysis): Only patients fully compliant with the protocol (especially regarding dosage) will be analysed. The full analysis set will be taken as safety analysis population as all patients will receive the study medication.

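### The sample size section names AUC of at least 0.70 as the alternative but takes N = 40 from the 0.75 row, so the 20% type II error does not apply at 0.70, where power is about 60% per tracer

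*Protocol*

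**What the plan says.** Protocol section 7.3, Sample size calculation, lists five assumptions. The fourth is "Type-I-error 0.05; type-II-error 0.20". The fifth is "True accuracy (AUC) is at least 0.70 (alternative hypothesis", supported only by a remark that some common diagnostic tests exceed that value. The case mix is "10% responder, 60% progressers; thus 40% non-progressers".

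The table below the list gives 64 patients (26 non-progressers, 38 progressers) at AUC 0.70, 40 (16 and 24) at 0.75, and 27 (11 and 16) at 0.80. The 0.75 row is in bold. The text concludes, on an assumed AUC of 0.75, that "40 patients are needed to reject the null hypothesis" of 0.5. It adds that this size gives a 95% confidence interval of half-width 0.17.

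The synopsis gives 40 patients, and section 3.2 makes that a ceiling: "It is planned to recruit a maximum of 40 patients over a 15 months period". The primary test in section 7.2 is an "intersection-union test at one-sided level 2.5" per cent.

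**The concern.** The list of assumptions and the conclusion use different alternatives. If the alternative is an AUC of 0.70 or more and the type II error is 0.20, the usual reading is that power is at least 80% over that whole range, so the lowest value, 0.70, sets the size. By the protocol's own table that means 64 patients. The trial is capped at 40, the number for 0.75. Nothing in the section explains the move, and the one piece of support offered is attached to 0.70.

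What is at stake is how a negative result is read. Someone who takes assumptions (4) and (5) together with N = 40 will believe that a tracer with a true AUC of 0.70 would be missed one time in five. If the real figure is nearer two in five, a non-significant result says much less against an AUC of 0.70 than the stated error rates suggest.

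**Working it through.** **Inputs.** From section 7.3: null AUC 0.5, type I error 0.05, type II error 0.20, 40% non-progressers and 60% progressers (k = 1.5 progressers per non-progresser). From section 7.2: one-sided 2.5%, which has the same critical value, 1.96, as two-sided 5%. The protocol cites textbook formulae without printing them. The formula below was chosen because it reproduces the protocol's figures.

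**Formula.** Binormal variance of the AUC, per non-progresser:

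V(A) = 0.0099 × exp(−a²/2) × [(5a² + 8) + (a² + 8)/k], with a = 1.414 × z(A)

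n (non-progressers) = [1.96 √V(0.5) + 0.84 √V(A)]² / (A − 0.5)², total = 2.5 n

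V(0.5) = 0.0099 × (8 + 8/1.5) = 0.132, so 1.96 √V(0.5) = 0.712.

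**Step 1: reproduce the protocol's table.**

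| AUC | V(A) | n non-progressers | Total | Protocol |
|---|---|---|---|---|
| 0.70 | 0.1237 | 25.4 | 63.5 | 64 |
| 0.75 | 0.1161 | 16.0 | 39.9 | 40 |
| 0.80 | 0.1042 | 10.8 | 26.9 | 27 |

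Half-width at 0.75: 1.96 × √(0.1161/16) = 0.167 (protocol: 0.17). Everything agrees. A one-sided 5% test would give about 50, 31 and 21 patients and does not fit, so the table was built with 1.96.

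**Step 2: power of 16 + 24 patients.**

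Power = Φ{[(A − 0.5) √16 − 1.96 √V(0.5)] / √V(A)}

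- At 0.75: Φ[(0.25 × 4 − 0.712)/0.341] = Φ(0.845) = 0.80.
- At 0.70: Φ[(0.20 × 4 − 0.712)/0.352] = Φ(0.250) = 0.60.

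The type II error at 0.70 is therefore about 0.40, twice the stated 0.20.

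**Step 3: how firm is 60%?** All figures are at AUC 0.70 with 16 and 24 patients and critical value 1.96.

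- Variance formulas that use the null variance under the null hypothesis, as the table does: 57% to 60%.
- Formulas that use the alternative variance under both hypotheses: 62% to 69%. In the binormal form this gives totals of 61, 37 and 23 and does not reproduce the table.
- Simulation of the nonparametric DeLong analysis named in section 7.4: 62% with equal standard deviations, 59% and 55% if the progresser standard deviation is 0.7 or 0.5 times that of non-progressers. The protocol states that "Variability in the PET-results of non-progressers is greater than that of progressers" but gives no ratio, so these ratios are assumptions.

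No variant comes near 80%. A one-sided 5% test would give about 72%, but it contradicts section 7.2 and does not reproduce the table.

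**Step 4: both tracers.** If the intersection-union test requires FDG and FLT both to be significant, joint power at 0.70 is 0.60 × 0.60 = 0.36 with independent test statistics and about 0.53 with a correlation of 0.9 between them. A separate simulation gave 39% to 52% for correlations of 0 to 0.8 between the two uptake values. The protocol gives no correlation, so all of these are assumptions.

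**The case against.** The best defence is that the protocol is open about its choice. It prints the 64-patient row, puts the 0.75 row in bold, and says in its conclusion that 0.75 is assumed. An AUC of at least 0.70 is a range that contains 0.75, so 0.70 can be read as the floor of the values explored and 0.75 as the design value. Nor does the protocol set a futility rule or say that a negative result counts against 0.70. The trial is labelled exploratory, and the confidence interval will show what remains compatible with the data.

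Much of this stands. A reader might infer that the calculation is wrong, or that the protocol claims 80% power at 0.70. The documents support neither: the arithmetic is sound and no such claim is made. A reader might also take 36% as the power of the trial. That figure needs independent test statistics, which the documents do not state, and it concerns a multiplicity question that the sample size section does not address.

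What does not stand is that openness settles the matter. Assumption (5) carries the label of alternative hypothesis, sits next to the type II error, and has the only justification given. Printing the 64-patient row shows the conflict without explaining it. The confidence interval helps at the reporting stage but does not correct the stated design error rate.

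**Conclusion.** The point holds as an inconsistency in how the design alternative is stated, not as an error of calculation. The 0.20 type II error belongs to AUC 0.75. At the lower limit of the named alternative, 0.70, it is about 0.40: single-tracer power is about 60%, with a plausible range of roughly 55% to 69%.

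This rests on a 16/24 split, all 40 patients evaluable, and one tracer. Each condition is favourable or neutral. No allowance is made for non-evaluable patients, although the full analysis set is "contingent on availability of endpoints", and needing both tracers to succeed would lower power further, by an amount the documents do not fix (about 36% to 53% at 0.70 for assumed correlations of 0 to 0.9).

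It does not follow that the trial must enrol 64 patients. Sizing for 0.75 is a legitimate choice if it is stated as such. The endpoint, the test and the number recruited are unaffected.

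**What to change.** In section 7.3, reword assumption (5) so that the design alternative is an AUC of 0.75, with a sentence on why that value was chosen. Beside N = 40, state that power for a single tracer is about 80% at AUC 0.75 and about 60% at 0.70, with 16 non-progressers and 24 progressers evaluable. Add that a non-significant result does not by itself exclude an AUC of 0.70.

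If the primary test is meant to require both tracers, say so there and note that joint power is lower. Any figure quoted for it should name the correlation assumed.

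The cost is one restated assumption and one less favourable figure in print. N does not change.
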